### Monitoring

This study will be performed by the approved protocol. It is supervised by a data and safety monitoring team appointed by the ethics committee of Ruijin Hospital, Shanghai Jiao Tong University School of Medicine. The data and safety monitoring team will review the data after 20%, 50%, and 80% enrollment to monitor the study progress and all AEs that may occur. Computer-generated and timestamped audit trials will also be implemented for tracking changes in the electronic source documentation to ensure the integrity of the research data.

### Safety and adverse events

Pantoprazole tablet has been used for more than 20 years, and the overall characteristics of its adverse reactions have been well described. This study mainly collects those AEs of particular concern related to PPI [20], such as chronic nephropathy, pathological fractures, myocardial infarction, pneumonia, spontaneous bacterial peritonitis, gastrointestinal tumors, and trace element deficiency. Non-serious AEs that did not cause discontinuation of the study drug will not be collected.

Participants showing any AE will be treated appropriately by doctors, and the project will cover the cost of AEs. Adverse reactions will be checked at every visit. For any AE that occurs, all details, including the time of occurrence, symptoms, signs, degree, duration, laboratory findings, treatment, outcomes, and causal relationship with the treatment, will be recorded in the CRF. Serious AEs will be reported to the Research Ethics Committee within 24 h, which will decide whether any additional measures should be taken. The total number of patients with AEs related to the study drug (certain, probable, possible) and the total number of patients with AEs leading to discontinuation of study treatment will be summarized.

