**Discussion:**

This study aims to compare the efficacy and safety of 12 months and 1 month of pantoprazole treatment in preventing DAPT-related upper gastrointestinal mucosal injury after CABG.

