### Intervention

Participants will be equally randomized into two groups: the experimental group (12-month treatment of pantoprazole) or the control group (1-month treatment of pantoprazole). Pantoprazole, 40 mg daily, will be used in combination with two different DAPT regimens (clopidogrel plus aspirin or ticagrelor plus aspirin), respectively. The study drug will be provided by Takeda (Shanghai, China). The detailed study schedule is listed in Fig. 2.

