### Follow-up

Patients will be followed up to 12 months post-randomization unless dead. The outcome will be collected at 2±1 day, 9±2 days, 1 month (30±7 days), 3 months (90±7 days), 6 months (180±14 days), 9 months (270±14 days), and 12 months (360±14 days) after CABG surgery, respectively. Among them, the visits at 3 and 9 months after randomization are telephone calls. Each subject’s survival status (surviving/deceased), blood pressure, heart rate, body mass index, waist circumference, and adverse events (AEs) will be recorded on the CRF after each conversation. At 6 and 12 months post-randomization, routine laboratory tests and anesthesia EGD will be performed respectively. The endoscopist in the present study who evaluated the upper GI mucosal injury was blinded to random treatment allocations. In addition, computed tomographic angiography (CTA) or coronary angiography (CAG) is also required at 12 months post-randomization. Face-to-face adherence reminder sessions will take place at the initial pantoprazole dispensing and each study visit thereafter.

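### The rules for collecting adverse events conflict, and the restrictive one would make non-serious AE counts non-comparable between the 12-month and 1-month arms

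*Protocol article*

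**What the plan says.** The section Safety and adverse events opens with the scope: "This study mainly collects those AEs of particular concern related to PPI". It lists examples such as chronic nephropathy, pathological fractures, pneumonia and trace element deficiency. It then restricts the scope: "Non-serious AEs that did not cause discontinuation of the study drug will not be collected".

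Three other statements carry no such limit:

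- Same section, next paragraph: "For any AE that occurs, all details, including the time of occurrence, symptoms, signs, degree, duration, laboratory findings, treatment, outcomes, and causal relationship" with treatment are to be entered in the CRF.
- Follow-up: "adverse events (AEs) will be recorded on the CRF after each conversation".
- Monitoring: the data and safety monitoring team reviews the data "to monitor the study progress and all AEs that may occur".

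Under Intervention, pantoprazole runs for 12 months in the experimental group and 1 month in the control group. Under Follow-up, both groups are followed for 12 months. Safety is part of the comparison: the Discussion paragraph of the Abstract says the study aims to "compare the efficacy and safety of 12 months and 1 month of pantoprazole treatment", and the end of the Background says much the same. The planned safety summaries are the number of patients with drug-related AEs and the number with AEs that led to stopping study treatment.

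**The concern.** Site staff cannot follow all of these statements. A non-serious AE that leaves treatment unchanged is either entered in the CRF or it is not. The monitoring team cannot review all AEs if one class is never collected.

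The choice also matters for the comparison. Under the restrictive sentence a non-serious AE is recorded only if it stops the study drug, and a patient who is taking no study drug has nothing to stop. Exposure to study drug is the randomized factor, so the chance of an event being recorded would differ by arm even if its true frequency did not. The trial is open-label, so the decision to stop drug, which triggers collection, is also made with the arm known.

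At stake is the non-serious part of the safety comparison. An excess in the 12-month arm could come from ascertainment alone, while non-serious harms that patients tolerate without stopping treatment could go unrecorded in either arm.

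**Working it through.** The article gives no AE rate, so there is no stated figure to reproduce. The contradiction needs no arithmetic. The size of the imbalance, if the restrictive sentence governs, can be bounded.

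**Inputs from the article**

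- Follow-up: 12 months, with the last visit at 360 days (Follow-up).
- Study drug: 12 months versus 1 month, the 1-month visit being at 30 days (Intervention, Follow-up).
- Planned size: 232 in a 1:1 ratio, so 232 / 2 = 116 per arm (Sample size).
- Controls who meet set criteria during follow-up receive a PPI after month 1 (Definition of the end of study). The article does not say whether this PPI counts as study drug.

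**Step 1: time in which a non-serious AE can qualify**

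- 12-month arm, while on drug: up to 360 / 360 = 100%.
- Control who stays off PPI: 30 / 360 = 8.3%.
- Ratio: 360 / 30 = 12 to 1.

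**Step 2: effect on recorded counts, with no true difference**

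Assume the same 12-month risk *p*, in both arms, of a non-serious AE that would stop the drug, with a constant hazard. The 12-month arm records a proportion *p*. A control off PPI records 1 − (1 − *p*)^(30/360). The values of *p* are assumptions, shown as a range.

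| Assumed *p* | 12-month arm, per 116 | Controls off PPI, per 116 |
|---|---|---|
| 2% | 2.3 | 0.2 |
| 5% | 5.8 | 0.5 |
| 10% | 11.6 | 1.0 |
| 20% | 23.2 | 2.1 |

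For example, at 5%: 1 − 0.95^(1/12) = 0.0043, and 116 × 0.0043 = 0.5.

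**Step 3: allow for controls who take a PPI later**

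Suppose that this PPI counts as study drug. If a share *r* of controls starts it at the 6-month endoscopy (day 180), the average control window is (30 + *r* × 180) / 360. If they continue from month 1, it is (30 + *r* × 330) / 360. The shares are assumptions.

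| Share *r* | Window, start at 6 months | Ratio to 12-month arm | Window, from month 1 |
|---|---|---|---|
| 18% | 17.3% | 5.8 to 1 | 24.8% |
| 36% | 26.3% | 3.8 to 1 | 41.3% |
| 50% | 33.3% | 3.0 to 1 | 54.2% |
| 100% | 58.3% | 1.7 to 1 | 100% |

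The imbalance shrinks but disappears only if every control stays on a PPI from month 1, in which case the arms would no longer differ in treatment.

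**Step 4: under the unrestricted statements**

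If any AE is recorded at each contact, the window is 360 versus 360 days and this ascertainment imbalance does not arise. The count of AEs leading to discontinuation still depends on having drug to discontinue, whichever rule is used.

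**The case against.** The best defence reads the safety section in sequence. The listed PPI-related events are the main collection, with no limit by arm or seriousness. Other non-serious events are dropped unless they stop the drug. The any-AE sentence then describes how an in-scope event is documented. Limited collection is also a reasoned choice for a drug the article describes as in use for more than 20 years. The safety analysis is descriptive, with no between-arm test, and the main clinical harms are trial outcomes in both arms.

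Much of this stands, and it rules out three stronger readings that a reader might infer.

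- *That the safety comparison is biased by design.* The imbalance arises only if the restrictive sentence governs, and three other statements point the other way. The text establishes a conflict with a possible bias, not a bias already built in.
- *That no non-serious AE can qualify in the control arm after month 1.* This is true only of controls who stay off PPI. Some receive a PPI later, and its status as study drug is undefined.
- *That non-serious cases of the listed events are discarded.* That is one reading. The article can also be read as keeping them.

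The defence does not remove the conflict. The article nowhere exempts the listed events from the exclusion, and Follow-up and Monitoring do not confine themselves to in-scope events. Trace element deficiency shows why this matters: it may be non-serious and leave treatment unchanged, and the laboratory tests named under Scope of study data do not mention trace elements. Descriptive reporting does not help either, because counts from unequal ascertainment mislead without a test. Nor is this detail left to a fuller document, since both rules are stated outright here.

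**Conclusion.** The AE collection rules contradict each other and must be reconciled. If the restrictive sentence was followed, non-serious AEs can be ascertained for up to about 360 days in the 12-month arm against about 30 days in controls who stay off PPI. At an assumed common risk of 2% to 20%, that means about 2.3 to 23.2 versus 0.2 to 2.1 recorded patients per 116. These counts assume a constant hazard, full exposure in the 12-month arm and no PPI in controls after month 1. Allowing for PPI started at 6 months brings the window ratio to between 5.8 to 1 and 1.7 to 1 over the assumed shares.

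On that reading, counts of non-serious AEs and of AEs leading to discontinuation are not comparable between arms. The count of drug-related AEs is affected to the extent that it includes non-serious events. The sentence does not exclude serious AEs. MACE, death and upper gastrointestinal bleeding are outcomes in both arms and are not affected. The sample size is not affected.

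**What to change.** Reconcile Safety and adverse events, Follow-up and Monitoring into one rule that does not depend on exposure. The listed PPI-related AEs of concern, serious or not, are recorded in both arms at every scheduled visit to month 12, whether or not study drug is being taken or stopped. State that serious AEs are collected in both arms for the same period, and say whether a PPI taken by controls after month 1 counts as study drug for AE purposes.

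Report AEs leading to discontinuation descriptively, by period (0–1 and 1–12 months), and draw no between-arm safety conclusion from them.

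State in the final report which collection rule was applied to patients already followed.

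The cost is a short amendment and some extra CRF entry at visits that are already scheduled. The repair is only partly prospective: Trial status reports that 117 patients had completed 12-month follow-up. If the restrictive rule was applied to them, their non-serious events will be incompletely captured, and a change of rule during the trial adds a before-and-after difference that the report should disclose.

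### The rule that drops non-serious AEs unless they stop pantoprazole has no written exemption for the listed PPI AEs; followed literally, it would record them differently by arm after month 1

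*Protocol article*

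**What the plan says.** Safety and adverse events opens its collection rule with "This study mainly collects those AEs of particular concern related to PPI" and gives examples: "chronic nephropathy, pathological fractures, myocardial infarction, pneumonia, spontaneous bacterial peritonitis, gastrointestinal tumors, and trace element deficiency". The next sentence is "Non-serious AEs that did not cause discontinuation of the study drug will not be collected". It does not say whether the examples just given are excepted.

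Three other places read more widely:

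- The same section later says "For any AE that occurs, all details, including the time of occurrence", with further particulars, goes into the CRF.
- Follow-up says "adverse events (AEs) will be recorded on the CRF after each conversation".
- Monitoring has the safety team review data "to monitor the study progress and all AEs that may occur".

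Under Intervention, the experimental arm takes pantoprazole for 12 months and the control arm for 1 month. Follow-up runs to 12 months in both. Statistical and analytical plans puts everyone with at least one dose in the safety set and makes the safety summaries descriptive. Two AE totals are named: patients with drug-related AEs, and "the total number of patients with AEs leading to discontinuation of study treatment will be summarized".

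**The concern.** Whether a non-serious AE is kept depends on whether it made the patient stop the study drug. A control who finished pantoprazole at month 1 has nothing left to stop and cannot meet that condition, although follow-up continues for 11 more months. A patient in the 12-month arm can meet it throughout.

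Comparing the safety of the two durations is a stated aim (Abstract, Discussion; end of Background). The events the article singles out are plausible costs of longer PPI use. If their non-serious forms are filtered by a condition tied to exposure, the recorded difference partly reflects time on drug and stopping habits. A statistical analysis plan cannot repair this, because the events would never have been collected.

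**Working it through.** The article gives no AE rate or discontinuation rate, so there is no figure of its own to reproduce. The sample size does not enter. The check is to trace one event through each reading, followed by an illustration on assumed inputs.

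**Step 1. One event, three readings.** Take a non-serious outpatient pneumonia at month 5.

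| Reading | Control, off pantoprazole | 12-month arm, drug continued | 12-month arm, drug stopped for it |
|---|---|---|---|
| Exclusion sentence applied literally | not recorded | not recorded | recorded |
| Listed events exempt from it | recorded | recorded | recorded |
| The any-AE sentences govern | recorded | recorded | recorded |

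Only the literal reading depends on arm, and the text does not say which reading holds. Some controls go back on a PPI under the criteria in Definition of the end of study. Whether that PPI counts as study drug is not stated.

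**Step 2. What is covered under any reading.** Serious AEs are reported in both arms. MACE (which includes myocardial infarction), death and upper gastrointestinal bleeding are outcomes in both arms (Outcome measurements). Renal function is measured in both arms at 6 and 12 months (Scope of study data), which partly covers nephropathy. Upper gastrointestinal tumours are sought in both arms by endoscopy at 6 and 12 months. That leaves mainly non-serious pneumonia, fracture, trace element deficiency and part of nephropathy.

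**Step 3. Illustration under the literal reading.** All rates are assumptions:

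- n = 118 per arm (236 enrolled, halved)
- p = 10%, the 12-month risk of a non-serious listed event, equal in both arms
- d = 20%, the share of on-drug events that stop pantoprazole
- f = share of events falling in month 1, the rest spread evenly over months 2 to 12
- r = share of controls restarting a PPI at month t, counted as study drug
- the 12-month arm stays on drug throughout

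The share of control events that occur on drug is S = f + (1 − f) × r × (12 − t)/11. Example: f = 1/12, r = 0.36, t = 6 gives 0.083 + 0.917 × 0.36 × 6/11 = 0.263.

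True patients per arm: 118 × 0.10 = 11.8. Recorded in the 12-month arm: 11.8 × 0.2 = 2.36, so 80% are lost. Recorded in controls: 2.36 × S.

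The recorded difference in percentage points is 0.2 × 10 × (1 − S) if the true risks are 10% and 10%. It is 0.2 × (10 − 5S) if they are 10% (12-month arm) and 5% (1-month arm).

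| f, r, t | S | Controls recorded | Controls lost (1 − 0.2S) | Difference, true 10 vs 10 | Difference, true 10 vs 5 |
|---|---|---|---|---|---|
| 1/12, 0, – | 0.083 | 0.20 | 98.3% | 1.83 | 1.92 |
| 1/12, 0.36, 6 | 0.263 | 0.62 | 94.7% | 1.47 | 1.74 |
| 1/12, 0.36, 3 | 0.353 | 0.83 | 92.9% | 1.29 | 1.65 |
| 0.3, 0.36, 6 | 0.4375 | 1.03 | 91.3% | 1.13 | 1.56 |

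With d = 10% the spurious difference under equal risk is 0.56 to 0.92 points; with d = 50% it is 2.81 to 4.58. Counts scale with p: 1.2 vs 0.1–0.5 at 5%, and 3.5 vs 0.3–1.5 at 15%. In each row, the recorded data hardly separate no true difference from a true 5-point excess.

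**The case against.** The strongest reply is that the first sentence already says the listed events are collected, so the exclusion naturally applies to the remaining non-serious AEs. Otherwise the first sentence would do little for non-serious events. The any-AE sentences also describe collection that does not differ by arm. This is a fair reading, and under it the asymmetry for the listed events vanishes. It remains unwritten, however: saying what a study mainly collects is not an exemption from the sentence that follows.

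The article also condenses a full protocol (version 4.0), and site staff work from that protocol, the CRF and CRF training. So it cannot be said that staff do not know what to record. What stands is that the article states a rule and contradicts it elsewhere, which is more than leaving out detail.

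The illustration is assumption throughout. The 36% restart share borrows the assumed incidence of severe erosions and ulcers from Sample size, whereas the actual PPI restart criteria are different. The illustration shows direction and scale under one reading and does not estimate anything in this trial.

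A reader might infer that AE collection here does differ by arm and that the safety comparison is biased. The documents do not support that, because two of the three readings are neutral between arms and actual practice is not reported. Nor do they support calling the two named AE totals wrong. These are conventional summaries, no test on them is planned, and the article does not present them as a between-arm comparison.

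**Conclusion.** The point holds as a defect of wording with a conditional consequence. The exclusion sentence has no written exemption for the listed PPI events and conflicts with Follow-up, Monitoring and later text in its own section. If it is followed literally, the descriptive comparison of 12 months with 1 month is distorted for non-serious listed events after month 1.

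The size cannot be known from the article: about 1.1 to 1.8 points of spurious excess in the central illustration, and nil for the listed events if an exemption was intended. The events covered in both arms (Step 2) and the primary result are untouched. Severity: minor.

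**What to change.** Through the route in Amendment, replace the exclusion sentence with wording such as: *Serious AEs, and the AEs of particular concern listed above, are collected in both arms for the full 12 months, whatever their seriousness, judged causality or effect on study drug. Other non-serious AEs are collected only if they lead to discontinuation of pantoprazole.* Align Follow-up, Monitoring and the later any-AE sentence with that rule.

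Summarise serious and listed AEs by randomised arm, all-causality, in the safety set. Do not use the other non-serious AEs for comparison between arms after month 1, since their collection still depends on stopping the drug.

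The wording costs little, but the change comes late. Per Trial status, 236 were enrolled, 183 had an effective intervention and 117 had completed 12 months. The article does not say that the completers all belong to the 183, and the safety set is wider than the 183. Of those already enrolled, between 183 − 117 = 66 and 236 − 117 = 119 could still have follow-up left, many only part of it; later additions come on top. If practice before the amendment differed, show events recorded before and after it separately. If practice already treated the listed events as exempt, nothing recorded need be discarded.

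Even complete collection would be imprecise: at an assumed 10% risk and 118 per arm, the 95% half-width is 1.96 × √(2 × 0.10 × 0.90/118) = 7.7 points. The comparison stays descriptive.

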### Amendment

All proposed protocol changes will be recorded in a protocol amendment, and this will be submitted to the Committee of Ethics and the regulatory authority for approval.

## Discussion

Our previous study (DACAB-GI-1), a single-center prospective substudy of a RCT (DACAB, NCT02201771) [20], provided important reference data for the subsequent design of the DACAB-GI-2 trial. Briefly, patients aged 18–80 years with indications for elective CABG surgery were randomized to 1 year of open-label antiplatelet therapy comprising ticagrelor 90 mg twice daily plus aspirin 100 mg enteric-coated tablet, once daily; ticagrelor alone (90 mg twice daily); or aspirin alone (100 mg once daily). Prophylactic use of PPI was not a randomized intervention. It was recorded at 1, 3, 6, and 12 months post-CABG. Data of both upper gastrointestinal mucosal injury assessed by EGD and *H. pylori* infection detected by ^13^C urea breath test were obtained only at 1 year post-CABG, not at baseline [12]. In the present study (DACAB-GI-2), 232 subjects on DAPT after CABG will be randomized into two treatment groups (12- vs. 1-month treatment of pantoprazole); ^13^C urea breath test is done before enrollment and EGD is performed at 6 and 12 months after randomization, respectively.

A PPI selected in the present study was pantoprazole. Compared with the other PPIs, pantoprazole has a lower affinity for CYP2C19 and has the least interaction with other kinds of drugs, so it has higher safety and is less likely to cause AEs in patients when used in combination with dual antiplatelet agents [6, 7]. Whether the P2Y_12_ receptor inhibitor is clopidogrel or ticagrelor, pantoprazole is suitable in combination with it. In the present study, all patients will be treated with pantoprazole for at least 1 month after CABG to reduce the risk of perioperative gastrointestinal bleeding.

Patients undergoing CABG are those with more advanced coronary artery disease. EGD will not be performed preoperatively, perioperatively, and within 6 months of surgery, except in cases of emergency [21], because it is not considered to be in the patients’ best interest. In the present study, EGD will be performed at 6 and 12 months after randomization. The purpose of designing the first EGD at 6 months is not only to establish self-control but also to help identify patients with asymptomatic ulcers on time. Of particular importance, the early stages of esophageal and gastric neoplasms are asymptomatic as well. These patients are considered to have reached the endpoint of the study if they are diagnosed by EGD and biopsy at 6 months post-randomization.

The present study includes two subgroup analyses, one is *H. pylori* infection status and the other is DAPT treatment. The results of our DACAB-GI-1 study [12] showed that the positive rate of *H. pylori* in patients receiving 1 year of antiplatelet therapy after CABG was 38.5%. After the study is completed, patients will be divided into the *H. pylori*-positive group and the *H. pylori*-negative group based on the results of the ^13^C urea breath test before enrollment; in addition, patients will be categorized into the clopidogrel plus aspirin group and the ticagrelor plus aspirin group according to their DAPT regimen after CABG. The difference of the primary and secondary endpoints will be compared in the above two subgroup analyses, respectively. Recently, the OPT-PEACE study [22] revealed the presence and severity of gastrointestinal mucosal lesions at 6 months or 12 months by magnetically controlled capsule endoscopy in patients receiving 12-month DAPT without PPI after PCI. To date, no study has reported visually evaluating the upper gastrointestinal mucosal injury (including RE) after 6 and 12 months of PPI treatment combined with two different DAPT by EGD yet.

In conclusion, the present study (DACAB-GI-2) probes the difference in preventing DAPT-related upper gastrointestinal mucosal injury after CABG between the different durations of pantoprazole treatment. The results should provide some confirmatory evidence for studies in relevant fields.

